### Eye movement desensitization and reprocessing (EMDR)

Participants allocated to the EMDR + TAU group will receive a manualized intervention. This set of EMDR protocols was developed by the principal investigator and the EMDR International Association (EMDRIA)-approved consultant involved in this study as a trainer. It incorporates elements of existing EMDR addiction protocols [35,37,38], related work [51] and insights on positive and prospective memory representations [19,20]. Based on pilot treatments, the intervention manual was fine-tuned before the recruitment phase.

Participants receive a maximum of seven weekly, 90-minute EMDR sessions provided by health care psychologists (who at least completed an EMDRIA-approved Basic Training program). The EMDR therapists will be trained in the use of the intervention manual and will be supervised monthly by the EMDR consultant. All EMDR sessions are video-recorded for fidelity rating and supervision.

Session one starts with instruction on some rules and the rationale for EMDR and its use in addiction. Then the treatment goal (controlled drinking or abstinence) is established. Subsequently participants are instructed to imagine their positive treatment goals vividly. After that both negative associations with long-term abstinence (if present) and positive memories associated with alcohol use are targeted with EMDR. At the end a homework diary is presented and participants are instructed to keep it daily, between sessions. It helps to register daily craving, alcohol use, possible adverse and/or positive events and help participants to prepare for the next session by identifying possible targets. Subsequent sessions focus on memory representations associated with loss of control, self-efficacy undermining beliefs, trigger situations, and anticipated relapse. Finally the focus shifts to feeling more empowered in trigger situations. Therapists are instructed to keep the duration of sessions as constant as possible, selecting only the most relevant targets. In some cases, fewer sessions may be required and provided.

### Termination of treatment

Regarding EMDR treatment, completers are defined as completing five or more of the scheduled seven EMDR sessions, allowing for some flexibility on the basis of clinical need. Those who attend four EMDR sessions or fewer for any reason comprise a premature termination of treatment (PTT) group.

Regarding TAU, a similar distinction is made whereby a completer attended five or more weeks of treatment (at least one face-to-face contact weekly) between T0 and T1 while those who attend four weeks or less of TAU fall in the PTT category.

### Data collection

Subjects participate in the study for 8 months (from T0 to T3). Patients in both treatment conditions will be assessed identically (see Table 1). Two instruments are only used during the inclusion interview: the MINI-Plus [43] and the MATE 2.1 [44]. At T0, RA1 (blinded to treatment allocation) assesses baseline measurements of all primary, secondary, tertiary and quaternary variables. At T1 (post treatment), T2 (follow-up after 1 month) and T3 (follow-up after 6 months) all but one (the ‘readiness for change’ as measured with the RCQ-D [52] is only assessed at baseline) measurements are repeated by RA1.

For participants in the EMDR + TAU group additional assessments take place within (pre and post levels of distress, craving or positive affect of memory representations on a 11-pt Likert scale) and between (daily diary: number of drinks, intensity and frequency of craving, adverse events) sessions. These assessments are an integral part of the EMDR intervention manual and can therefore only be used to explore changes during the course of EMDR within this group. EMDR therapists also fill in a questionnaire after the last EMDR session of each participant regarding perceived and experienced treatment burden credibility and harm, before, during and after treatment.

RA1 also gathers demographic data: age, sex, social-economic and marital status, educational level, and ethnicity. Participant-report questionnaires (no 3–11 in Table 1 below [6,52-59]) will be provided digitally using Perseus web survey software [60]. The alcohol Timeline Followback interview (TLFB; [61]) is conducted face-to-face by RA1.

The alcohol Stroop [62] and valence IAT [63] will be administered using the program Inquisit 3 [64] for computerized assessment.

After each on-site assessment, participants are referred to a laboratory nearby for collection of blood samples to determine GGT and CDT [65]. Results are interpreted by an independent physician from IrisZorg. The results will be discussed with the participants after the last assessment by this physician, if relevant. In the case that lab results merit intervention before the last follow up assessment, the physician will notify the regular addiction care physician or general practitioner as soon as possible.

### Instruments

#### Measurements - inclusion

##### Measurements in the addictions for triage and evaluation (MATE 2.1 [44])

The MATE is composed of 10 modules made up of a set of existing psychometrically validated short instruments from the public domain. In this study, RA1 only uses parts 1–4 to screen for eligibility criteria.Module 1: ‘USE’, is an interview used to determine the severity of the use of psychoactive substances in the previous 30 days as well as life-time. Inventarisation of substances (including nicotine and gambling), the level of use and typical form or route of application are reported. Use (in standard units) in the past period and use on a typical day of use are reported, as well as the number of years of regular use. The primary problem substance or behaviour is identified.Module 2: ‘INDICATIONS PSYCHIATRIC OR MEDICAL CONSULT’. Medical themes interviewed: 1) use of medication for addiction; 2) use of medication for other somatic complaints; 3) symptoms that may be the result of severe physical health problems; 4) intoxication or (severe) withdrawal symptoms; and 5) pregnancy. Psychological/psychiatrical themes interviewed: 1) current and recent psychiatric or psychological treatment; 2) use of medication for psychiatric reasons; and 3) suicide risk and psychotic symptoms.Module 3: ‘ADDICTION TREATMENT HISTORY’. This part of the interview questions whether and if so how much previous addiction treatments the participant has undergone in the past 5 years.Module 4: ‘DEPENDENCE AND ABUSE’. The questions are derived from the section Alcohol & Drugs from the CIDI (Composite International Diagnostic Interview) 2.1 [66] in accordance with the diagnostic criteria for substance abuse or dependence of the DSM-IV-TR [41]. In this study, the questions will relate to alcohol use since this will be the primary problem substance.

##### Mini-international neuropsychiatric interview (MINI-plus [43,67])

This brief, structured interview allows for the coding of more than 60 variables, including DSM-IV-TR disorders (23 axis 1 disorders) and suicide risk at the time of the interview or at some time in the past. Psychometric evaluation of the English version of the MINI (a less detailed version of the MINI-plus) showed that inter-rater reliability is good while test-retest reliability is satisfactorily, expect for current manic episode. Most scales possess a satisfactory degree of predictive power but positive predictive power for lifetime bulimia nervosa, social phobia and generalized anxiety disorder is relative weak [68]. Content validity of simple phobia and generalized anxiety disorder, when compared to the CIDI [66], was also low.

The MINI-Plus employs different time frames for various disorders: current, past, or lifetime. For screening purposes, we will only focus on the ‘current’ timeframe.

#### Measurements – effects on drinking behavior

##### Alcohol use disorders identification test (AUDIT; [53,69]

The AUDIT is a 10-item, self-report measure assessing harmful alcohol consumption (items 1 to 3), drinking behavior (items 4 to 6), adverse reactions to alcohol (items 7 to 8), and alcohol-related problems (9 to 10). Scores on items 1 to 8 can range from 0 to 4, while items 9 and 10 are scored 0, 2, or 4. Higher scores indicate higher risk and range from 0 to 40. Scores between 8 and 12 indicate hazardous or harmful alcohol use, while scores 13 to 40 indicate likely alcohol dependence [70,71]. A high reliability, sensitivity, and specificity of the scale has been reported [53].

The timeframe normally used is that of the previous year. However, since we want to repeat the AUDIT assessment, this time frame would cause overlap between assessments. Therefore we will use a time-frame of 1 month.

##### Alcohol timeline followback (TLFB [60])

The Alcohol TLFB is a drinking assessment method that obtains estimates of daily drinking and has been evaluated with clinical and non-clinical populations. Using a calendar, people provide retrospective estimates of their daily drinking over a specified time period that can vary up to 12 months from the interview date. In this study retrospective estimates of the previous month will be used. Several memory aids can be used to enhance recall (e.g., calendar; key dates serve as anchors for reporting drinking; standard drink conversion). The Alcohol TLFB has been shown to have good psychometric characteristics with a variety of drinker groups, and can generate variables that provide a wide range of information about an individual’s drinking (e.g., pattern, variability, and magnitude of drinking). The method is recommended for use when relatively precise estimates of drinking are necessary, especially when a complete picture of drinking days (i.e., high- and low-risk days) is needed (evaluating drinking pre-posttreatment). Although Timeline summary data have been found to be generally reliable, as with all drinking assessment methods, exact day-by-day precision cannot be assumed or necessarily expected. Overall, the Alcohol TLFB method provides a relatively accurate portrayal of drinking, and has both clinical and research utility.

##### Serum γ-glutamyltransferase (GGT) and carbohydrate-deficient transferrin (CDT)

CDT is currently the most specific marker of alcohol abuse, and when combined with GGT using an equation [0.8*ln(GGT) + 1.3*ln(CDT)] a high sensitivity is reached without loss of specificity [64]. The Dutch multidisciplinary protocol for alcohol problems [72] also states that assessment of CDT levels, which may be combined with those of GGT, is suitable to monitor reduction of or abstinence from (chronic) alcohol use;

#### Measurements – mediators, moderators and predictors of treatment outcome

##### Readiness to change questionnaire (RCQ; [52,73]

The RCQ is an instrument which tries to capture the stage of change the patient is in, according to the stages of change model [74]. The RCQ has 12 items which have to be answered on a 5-point scale. There are three subscales reflecting pre-contemplation, contemplation and action. The instrument has a satisfactory internal consistency and, in most studies, a satisfactory test-retest reliability ([73], p. 752). The predictive validity of the original instrument is sufficient: the RCQ predicts changes in drinking behavior [75]. However, one study found that there was little agreement between self- and interviewer rating of the alcohol version of the RCQ and between self-report on different instruments relating to the same concepts [76].

The psychometric quality of the RCQ-D (translated by [73]) seems comparable to the original. Some negative formulated questions were transformed into positive formulations. Although the underlying transtheoretical model has been criticized [77], the questions in itself can provide insight into the motivation for change and drinking related appraisals at the moment of assessment. The instrument can assist in distinguishing those patients who are ready to change their drinking behavior and those who are probably in need of further motivational counseling [73].

##### Penn alcohol craving scale (PACS; [57])

The PACS is a measure of weekly craving. The PACS was selected because prior research has demonstrated the PACS to have greater predictive value for treatment outcomes compared to the Obsessive–Compulsive Drinking Scale or the Alcohol Urge Questionnaire [78]. The PACS consists of five items each scored 0–6 in increasing severity of craving.

The PACS has excellent internal consistency [57]. Predictive, construct, discriminant validity was demonstrated. The PACS is a reliable and valid measure of alcohol craving and can predict which individuals are at risk for subsequent relapse. Although the instrument has not been translated and validated in the Netherlands, we believe the brevity and psychometric qualities of the original instrument makes it suitable for the current study. A Dutch version (translated by two independent researchers and discussed after which consensus was reached on a final translation) was used here.

##### Desire thinking questionnaire (DTQ; [6])

The DTQ is based on the elaborated intrusion theory of desire [79]. Items are scored on a 4-point Likert-type scale (“Almost never”, “Sometimes”, “Often” or “Almost always”). Although the DTQ uses no timeframe, here we focus on the previous month in order to make sure there is no overlap in timeframe between subsequent assessments. Differentiated in a total score (10 items × 1–4 points (range 10–40 points)) and subscores for the factors Verbal Perseveration and Imaginal Prefiguration (5 items × 1–4 points (range 5–20 points)). The first factor relates to ‘repetitive self-talk regarding the need to achieve the desired target and self-motivated statements’. The latter relates to the ‘construction of mental images of the desired target or of its context of consumption.

Psychometric evaluation demonstrated an acceptable level of internal consistency [6]. A moderate correlation between desire thinking, craving and rumination indicated that these concepts can be considered as divergent constructs. Test-retest reliability for both factors (.66 and .56) and total score (.59) was acceptable.

Predictive validity was determined in a sample of alcohol abusers seeking treatment from a variety of alcohol services (n = 78). Both DTQ factors correlated positively and significantly with craving, but only ‘Verbal Perseveration’ correlated positively and significantly with the level of alcohol use (but did not predict level of alcohol use in addition to the variance explained by craving). DTQ factors predicted craving independently of level of alcohol use.

##### Positive and negative affect schedule – short form (PANAS-SF; [58]

This 10-item instrument is a translated, Dutch version of the International PANAS-SF (I-PANAS-SF; translated from English by comparing it to the validated 20-item Dutch version of the PANAS [80], itself a translation of the original English version of the PANAS [81]).

Each item refers to a mood state and participants rate the extent to which each mood state describes how they feel at the moment of testing on a scale ranging from 1 (never) to 5 (always). It captures two dimensions of mood: positive and negative affect. Low positive affect (PA) corresponds to lethargy and sadness, whereas high PA reflects high energy, concentration and pleasurable mood states. Negative affect (NA) refers to distress and unpleasurable mood states, with low NA reflecting a state of calmness and serenity. One study demonstrated adequate reliability of the PA and NA subscales of the I-PANAS-SF [81]. The instrument compares well with the full 20-item original of both correlating with the original full form and temporal stability. Although the validity of the instrument in relation to stress and psychopathology needs to be determined, the brevity and straightforwardness of the instrument make it useful for repeated measurements, especially in the multiple baseline study. In addition, both PA and NA seem to play a role in conferring risk and maintaining substance use [11]. Most short affect measures only capture aspects of NA.

##### Perseverative thinking questionnaire (PTQ; [59]

The 15-item PTQ was recently developed to provide a content-independent measure of repetitive negative thinking (RNT). Preliminary validation supported lower order factors representing 1) the core characteristics of RNT (repetitiveness, intrusiveness and difficulties with disengagement), 2) perceived unproductiveness of RNT and 3) RNT capturing mental capacity. The PTQ shows good reliability and validity and recently a Dutch version was validated [82]. Each item is rated on a 5-point scale ranging from 0 (never) to 4 (almost always). No timeframe is used.

##### Alcohol stroop (derived from classic Stroop test [62,83])

A modified, computerized Stroop color-naming task with alcohol-related words (alcoholic drinks) as well as neutral (non-alcoholic drinks) words is used. The stimulus words are presented on a 17 inch laptop (using Inquisit 3 desktop software) in 4 different colors (yellow, red, green and blue). Participants view 3 screens (each representing a matrix of 5 columns and 8 rows, equaling a set of 40 stimuli) with different stimulus sets in a randomized, counterbalanced (between subjects) fashion: a) 4 × 10 alcohol-related words (beer, wodka, wine, rum, port, cognac, whiskey, gin, liqueur and jenever), b) 4 × 10 neutral words (7-up, orange juice, apple juice, cola, Fanta, cassis, water, lemonade, spa, Pepsi) or c) 40 non-words (series of colored XXX). This amounts to 1 trial per set. Each of the ten selected words is presented four times per set in a fixed order. The order of the colors is fixed as well. The same word or ink color does not occur more than twice in a row. All stimuli appear in lowercase Arial font (regular). The font size is 14. The projected stimuli appeared on the computer screen as color words presented against a black background.

This task allows assessment of interference (on attentional processing) due to alcohol cues. Shorter response latencies on alcohol-related rather than neutral words are assumed to indicate a stronger alcohol-related bias. In the version used here, participants are required to respond vocally to stimuli. Participants only name the ink color, reading as fast as possible from left to right and from top to bottom. Timing was done manually: directly after the last ink-color is named, the experimenter clicks the mouse, recording the total time per set. Number of errors are recorded manually by the experimenter. Both the alcohol-related and neutral scores are corrected by subtracting the non-word score.

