### Mediators, moderators and predictors of alcohol use and relapse

Addiction can be conceptualized as a cyclic process of anticipation, intoxication, and withdrawal [3]. The anticipation stage is considered a key element of relapse and often takes the form of intense craving. Craving refers to a compelling or intense urge, desire or intention to ingest a drug [4]. High baseline levels of alcohol craving may define a subtype of alcohol dependence that is less responsive to treatment and predict the chance of relapse after discharge [5]. In addition to craving itself it may be interesting to look at related concepts, such as desire thinking and rumination, which seem to augment craving.

Desire thinking refers to the elaboration of cognitions and imagery in working memory which may escalate craving intensity [6]. It correlates with escalating levels of drinking status [7]. Desire thinking is regarded as a specific type of perseverative thinking, such as rumination or worry [6]. Interestingly, rumination predicts long term outcomes of addiction treatment in alcohol-dependent patients [8]. Rumination increases craving in alcohol-dependent drinkers but not in problem and social drinkers [9]. So both desire thinking and rumination increase or intensify craving. Since rumination results in increased negative affect [10], it is no surprise that both low positive and high negative affect are associated with relapse in addiction [11]. So when levels of desire thinking and rumination are reduced, craving and negative affect may also be reduced, which would result in lower relapse rates.

In addition to these subjective processes, automatic implicit processes such as attentional biases have also been implicated in the maintenance of addiction [12,13]. Since alcohol attentional biases have a reciprocal excitatory relationship with craving, reductions in attentional bias should predict reductions in craving and drinking behavior. Whereas craving, desire thinking, rumination and negative affect are typically measured by subjective participant report, the strength of implicit processes may be measured more objectively in paradigms using changes in reaction times as primary outcome.

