#### Secondary objectives – mediators, moderators and predictors of treatment outcome

To explore mechanisms of change, variables that are potential predictors, mediators or moderators of treatment outcome will be examined (see Table 1). We distinguish:Dependent variables:Psychological (participant report): desire thinking, craving, rumination, negative affect and coping self-efficacy,Psychological (reaction times): alcohol attentional bias and implicit associations towards alcohol cues.Covariates:Measured at baseline: demographic characteristics, time-in-treatment, comorbid psychopathology, alcohol consumption, alcohol dependence severity, other substance use and readiness to change;Measured between baseline and follow-up: completer status, time-in-treatment, treatment intensity, the use of psychopharmaca, anticraving (naltrexone and acamprosate) or alcohol abstinence enforcing medication (disulfuram).

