### Power and sample size calculation

Since two active treatment arms are compared and the sample is expected to be relatively heterogeneous regarding baseline variables such as dependence severity, drinking status and other substance use, it is estimated that the effect size will be relatively small. Clinical relevant differences on the primary outcome variable (changes in number of heavy drinking days in the previous 30 days) were calculated on the basis of data of a recent study [46]. In patients with an alcohol-use disorder referred to in- or outpatient alcohol treatment the mean baseline score for heavy drinking days (≥5 drinks in a single day, over the past 30 days) was 16.33 (SD 11.99). Treatment outcome was such that undertreated patients (<75% attendance of the number of sessions recommended by treatment allocation guidelines, n = 618) showed a reduction of 8.7 heavy drinking days (±12.5) while overtreated patients (>110% attendance of sessions recommended) showed a reduction of 12.5 heavy drinking days (±12.2, n = 362). The difference between under- and overtreated patients is at least 3.8 heavy drinking days over the past 30 days which corresponds to an effect size of *d* = 0.31 or *f* = 0.15).

Subsequent poweranalysis in G*Power version 3.1.2. [47] (ANOVA: repeated measures, within-between interaction) indicated a sample size of 74 to demonstrate this effect (keeping α at 0.05 and power at 0.80 and using 2 groups and 3 measurements (concerning changes in the number of heavy drinking days between 4 time points)). Attrition is estimated to be relatively high at 33%. Therefore we add 26 participants (100 patients in total, 50 in each treatment arm), to meet the required sample size.

To minimize missing values RA1 will use email, text messages, telephone calls, and/or contacts with participants’ regular therapists to remind participants about their assessment appointments. All participants will receive financial compensation of 25 euros (in the form of a gift cheque) for every complete assessment at T2 and T3, regardless of whether or not the participant drops out of treatment.

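### The alcohol Stroop description reads shorter alcohol-word times as stronger bias, which contradicts its own account of the task as measuring interference

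*Protocol article*

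**What the plan says.** All the scoring information is in the Instruments part of the protocol article, under Alcohol stroop.

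- Construct: "This task allows assessment of interference (on attentional processing) due to alcohol cues".
- Response required: "Participants only name the ink color, reading as fast as possible from left to right and from top to bottom".
- Quantity measured: the experimenter clicks the mouse after the last colour is named, "recording the total time per set". Each set has 40 stimuli.
- Adjustment: "Both the alcohol-related and neutral scores are corrected by subtracting the non-word score".
- Interpretation: "Shorter response latencies on alcohol-related rather than neutral words are assumed to indicate a stronger alcohol-related bias".

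Two other places give the direction its importance. The Background section on mediators, moderators and predictors expects that "reductions in attentional bias should predict reductions in craving and drinking behavior". The Secondary objectives section lists, among the dependent variables based on reaction times, "alcohol attentional bias and implicit associations towards alcohol cues". Table 1 shows the alcohol Stroop as the only instrument for attentional bias, measured at T0, T1, T2 and T3.

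**The concern.** The interpretation sentence directly follows the sentence that defines the construct, and the two point in opposite directions. The word is irrelevant to the response, because the participant only has to name its colour. If alcohol words capture attention, colour naming slows and the alcohol set takes longer. A shorter alcohol-set time therefore means less interference, yet the article reads it as more bias.

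The direction matters because the article has a directional hypothesis: lower bias should go with less craving and less drinking. An analyst or reader who follows the sentence would read a reduction in interference as a worsening, and would find the expected positive association with craving and drinking to be negative. As no final bias index is given, this sentence is the only published rule for interpreting the measure.

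**Working it through.** No sample size, power or alpha depends on this point, so there is no figure of the plan to reproduce. The check is one of logic and sign.

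**1. Inputs (section Alcohol stroop).** Let T_alc, T_neu and T_non be the total times for the alcohol, neutral and non-word sets. A higher value means slower naming.

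**2. Corrected scores.** A = T_alc − T_non and B = T_neu − T_non. Subtracting the same quantity from both leaves their order unchanged.

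**3. Index implied by the construct.** Interference due to alcohol cues is A − B = (T_alc − T_non) − (T_neu − T_non) = T_alc − T_neu. The non-word time cancels. Larger means more interference.

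**4. Index implied by the interpretation sentence.** If shorter alcohol times relative to neutral mean stronger bias, patients are ordered by B − A = −(A − B). This is the exact negative of step 3 for any set of times.

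**5. Illustration.** The times are assumed, since the article gives none: non-word 25 s and neutral 30 s at both visits, alcohol 34 s before and 31 s after treatment.

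| | A | B | Interference, A − B | Bias by the stated rule, B − A |
|---|---|---|---|---|
| Before | 34 − 25 = 9 | 30 − 25 = 5 | 4 | −4 |
| After | 31 − 25 = 6 | 30 − 25 = 5 | 1 | −1 |

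Interference falls by 3 s, an improvement. By the stated rule bias rises by 3, a worsening.

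**6. What the sign changes and what it does not.**

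- The group-by-time F statistic is built from squared deviations. Multiplying the score by −1 leaves F and its p-value as they were; only the reading as benefit or harm reverses.
- The correlation of the score with craving or drinking keeps its size and changes sign.
- In a mediation model with path a (treatment to bias) and path b (bias to drinking), each path reverses. Their product does not, since (−a)(−b) = ab. The account of the mechanism along each path would be wrong, but the estimated indirect effect would not change.

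**7. Search for a rescuing reading.** Participants are not asked to detect or classify alcohol words, so faster responding to them is not the measured behaviour. No other section reverses the sign.

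**The case against.** A reader might infer that the trial scores the Stroop backwards and that a benefit of EMDR would be reported as harm. The article does not support that. The sentence is interpretive. The only scoring operation described is the non-word subtraction, which is neutral as to direction, and no bias index is defined. The scoring syntax and any analysis plan are not shown. A one-word slip, *shorter* for *longer*, fits the surrounding text at least as well as a deliberate reversed rule. This stands: misreporting is conditional on the sentence being followed.

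The measure is also peripheral. Attentional bias is one of several secondary variables meant to explore mechanisms. The Analyses section does not name it among the secondary variables for repeated-measures ANOVA, although that list gives examples and is not exhaustive. The primary outcome is change in heavy drinking days, and the sample size rests on that outcome alone ("The difference between under- and overtreated patients is at least 3.8 heavy drinking days over the past 30 days"). A reversed reading could also be put right later from the recorded set times. All of this stands and limits the consequence.

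Finally, no sentence in the article says outright that interference lengthens times. That step is the ordinary meaning of the word in a timed colour-naming task, and the article offers no other meaning. This point does not remove the contradiction.

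**Conclusion.** The sentence is wrong as written: it contradicts the task description in its own paragraph. Confidence in that is high. It is an incorrect statement, not a detail that an article may leave to a fuller document.

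The size is a full reversal in the reading of one secondary measure and in the sign of its associations with craving and drinking. There is no effect on the group-by-time p-value, the primary outcome, the sample size or the power. The reversal in results rests on one assumption that the article cannot settle: that the stated rule is carried into the scoring or the interpretation. The point should be corrected, but it does not threaten the trial's main conclusion.

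**What to change.** Replace *Shorter* with *Longer* in the interpretation sentence. Add that a larger corrected alcohol time relative to the corrected neutral time (alcohol minus neutral) means stronger bias, and note that the non-word correction cancels in this difference. If the two corrected scores are to be analysed separately instead, the same direction should be stated for their comparison.

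Then confirm, before analysis, that the scoring syntax and the planned interpretation agree with the corrected sentence. The Trial status section says recruitment was still under way, so this can be settled before results are known; a later change could look like a choice of sign made after seeing the data.

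The cost is one or two sentences and one check of the syntax. Data collection and the recorded times stay as they are.
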